### Criteria for discontinuing or modifying the allocated interventions {11b}

Criteria for discontinuing the allocated interventions are (1) disruptive behavior disorder that does not allow the child to benefit from the intervention; (2) behavior not stabilized by drugs for children under treatment; and (3) aggressive behavior of one participant toward the others.

The protocol does not allow modifying the allocated intervention.

### Strategies to improve adherence to interventions {11c}

To improve adherence to the intervention protocols, behavioral goals are defined to increase motivation. These challenges are individualized and focus on each child’s specific difficulties. At the session end, children must evaluate whether they have achieved their challenge. If the challenge is reached, they obtain a reward. Children learn that every effort deserves a reward.

During the study, participants will be contacted by telephone if absent during two consecutive sessions to know the reasons of their absence. Between sessions, caregivers are available by telephone or email to answer any questions from the families.

### Relevant concomitant care permitted or prohibited during the trial {11d}

During the interventions, pharmacological treatments are permitted. Moreover, pharmacological treatments can be modified if they are no longer appropriate. It is possible to begin a drug treatment during the trial if behavioral symptoms become too severe and have a negative impact on the child’s participation and implication in the group. The maintenance of other usual care components is authorized.

It is recommended that parents do not participate in other parental management training programs, because of similarities between the interventions proposed in the trial and those usually offered by care services.

### Provisions for post-trial care {30}

A participant may exit the trial for the following reasons: severe behavioral problems not sufficiently stabilized to allow the participant to benefit from the program, strong opposition to participate in the group, and inadequate behaviors (physical or verbal aggression against other participants or caregivers) that interfere with the proper functioning of the group. When a child behaves inappropriately (opposition, verbal or physical aggression, provocation…) during a session, a discussion time is offered with the child, parents, and caregivers. The objective is to find a solution together to solve the problem. This exchange may be enough to motivate the participant and stop the inappropriate behavior. Concomitantly, the child’s psychiatrist will be contacted and informed of the situation. He/she might decide to meet the child to modify the pharmacological treatment and to re-motivate him/her. Nevertheless, if the problematic behaviors persist and affect the group, the child exit from the program is decided together with the child, the family, and the psychiatrist.

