#### Exclusion criteria

Exclusion criteria are as follows: (1) child with delayed development or severe language disorder or autistism spectrum disorders; (2) parents who do not speak French; (3) lack of informed consent and assent by the parents and child for their participation in the study; and (4) child not living with at least one parent.

Delayed development was clinically assessed, but in a majority of cases, children also have psychometric tests to help exclude differential diagnosis and respond to administrative requirements for school compensations.

The majority of children included in this study follow regular school. However, children in specific structure school settings for disruptive behavior Educational and Pedagogical Therapeutic Institute will be accepted in this trial if they respond to eligibility criteria.

Study exit criteria are as follows: (1) participants lost to follow-up and (2) consent withdrawal by the parents. Each study exit will be explained and described in detail.

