### Outcomes {12}

Primary and secondary outcomes will be evaluated in the two groups (TBI and CBT) at the inclusion visit (baseline), at the end of intervention, and at month 6 after the end of the intervention.

The primary judgment criterion is the variation of the “Aggressive behaviors” score of the CBCL between baseline and month 6 post-intervention. The initial evaluation will be on outcomes at month 6 post-intervention; because we hypothesize that the effectiveness of such programs is observed several months after their end. Usually, it takes time for children and parents to assimilate and routinely implement the new techniques and also to observe the intervention benefits in the daily life. This will allow also assessing whether the beneficial effects of the interventions are maintained in the long term.

Secondary judgment criteria include also the variation between baseline and month 6 post-intervention of the CBCL A-A-A score, CBCL-Internalizing and CBCL-Externalizing scores, KIDSCREEN-27, Parental Quality of Life and Developmental Disorder (Par-DD-Qol), Children’s Global Assessment Scale (C-GAS), Parenting Stress Index-Short Form, 4^th^ edition (PSI-4-SF), Beck Depression Inventory-II (BDI-II), and Strengths and Difficulties Questionnaire (SDQ) and the SDQ-dysregulation profile (SDQ-DP).

Exploratory analyses will be realized and will concern the variation of primary and secondary judgment criteria between baseline and at the end of the intervention. Exploratory analyses will be realized to identify possible mediators concerning personality traits on therapeutic effects (response to treatment at T2).

Other data will be collected during the initial visit: presence or absence of psychiatric disorders in children using the K-SADS-PL diagnostic tool, sociodemographic data, anamnestic data, and medication history. Pharmacological treatments will be recorded at each visit because the introduction of a new drug or the modification of posology may influence the research outcomes. Indeed, ADHD usual treatment effectively reduces ED ([28, 46, 86]; Gamli et al., 2018 [97];). The Hierarchical Personality Inventory for Children (HiPIC) will be completed at the end of the intervention to limit the duration of the initial visit.

Means, standard deviations or frequencies, median and percentages will be calculated in order to describe sociodemographic and clinical variables of the sample as well as primary and secondary outcomes.

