### Participant timeline {13}

Outcome measures are collected at pretreatment (T1), just after treatment end (T2), and at month 6 post-treatment (T3) (Table 1). Data for the primary and secondary outcomes will be collected at child psychiatry unit of Montpellier University Hospital (MPEA Saint Eloi). The child presence is not required for all the measures collected during these assessments.

**Table 1 Tab1:** Visits and data acquisition during the trial

Timepoint	Study period			
	Enrollment	Before the intervention (T1)	At the intervention end (T2)	Six months after the intervention (T3)

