#### Primary outcome

##### Child Behavior Checklist (CBCL [3];)

The CBCL is a 118-item parent-completed questionnaire to measure emotional and behavior problems in 4- to 18-year-old children in the past 6 months. Parents rate each item as 0 (not true), 1 (somewhat or sometimes true), or 2 (very true or often true). The CBCL includes eight syndrome scores: Anxious/Depressed, Withdraw/Depressed, Somatic Problems, Social Problems, Thought Problems, Attention Problems, Rule Breaking, and Aggressive Behavior. A computer program calculates the *T*-scores for each scale. Raw scores are converted to gender- and age-standardized scores. A *T*-score of 50 indicates average functioning and standard deviation is every 10 points.

The objective of the primary outcome is to assess the effectiveness of the CBT program on the “Aggressive behavior” score (i.e., primary outcome) of the CBCL A-A-A. The CBT program should allow reducing aggression.

The “Aggressive behavior” sub-score contributes to the CBCL-DP and “Deficient Emotional Self-Regulation” (CBCL-DESR). The two profiles are the sum of the CBCL “Anxious/Depressed,” “Attention Problems,” and “Aggressive Behavior” (A-A-A) syndrome *T*-scores [3]. The CBCL-DESR is present when the sum of the CBCL A-A-A scores is ≥ 180, but below 210 (*T*-scores > 60). The “Dysregulation Profile” is present when the sum of the CBCL A-A-A scores is ≥ 210 (2 SD; *T*-scores > 70). These profiles represent a continuum of the emotional and behavioral dysregulation severity [14, 55]. They allow defining an ED phenotype and are a risk marker of a persisting deficit of self-regulation of emotion and behavior [40]. CBCL-DP and CBCL-DESR allow identifying a group of children with disruptive behavior [4] and at risk of severe dysfunction [30, 40, 79]. The CBCL-DP and CBCL-DESR profiles are associated with higher risk of comorbidities [27, 40, 55], hospitalization in psychiatry services [27], and development of inappropriate personality traits [67] in adulthood. The CBCL-DESR profile is a predictor of increased risk of opposition defiant disorder, conduct disorder, and anxiety disorders [79]. The CBCL-DP predicts high risk of mood disorders during adolescence [54].

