### Methods in analysis to handle protocol non-adherence and any statistical methods to handle missing data {20c}

Analysis of the primary and secondary outcomes will be carried out per protocol for all families who participated in two thirds of the intervention.

For missing data, under the hypothesis of a Missing at Random (MAR) or Missing Completely at Random (MCAR) mechanism, an imputation method using the Markov chain Monte-Carlo method will be used with 15 imputation cycles. The analysis will be performed independently for each complete database and the results will be taken into account for estimating the final parameters and their standard deviations.

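### The protocol contradicts itself on whether a child removed for aggression leaves the intervention or the trial, so primary outcome scores may be lost for reasons tied to that outcome

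*Protocol article*

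**What the plan says.** All references are to the protocol article; T1, T2 and T3 are used as in its Table 1.

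- **Exclusion criteria.** "Study exit criteria are as follows: (1) participants lost to follow-up and (2) consent withdrawal by the parents". No behavioural ground appears.
- **Section {11b}, on stopping the intervention.** Its text begins: "Criteria for discontinuing the allocated interventions are (1) disruptive behavior disorder that does not allow the child to benefit from the intervention". Behaviour not stabilised by medication and aggression towards other participants follow as further grounds. All three concern the intervention; leaving the study is not mentioned.
- **Section {30}, on care after the trial.** Its text begins: "A participant may exit the trial for the following reasons: severe behavioral problems not sufficiently stabilized to allow the participant to benefit from the program". The list continues with strong opposition to taking part and "inadequate behaviors (physical or verbal aggression against other participants or caregivers) that interfere with the proper functioning of the group". The same paragraph closes by describing departure from the program, not the trial, as a joint decision of child, family and psychiatrist.
- **Participant retention {18b}.** T2 and T3 visits are scheduled, families who are hard to reach are called repeatedly, and telephone completion is allowed in exceptional cases. The request to complete final questionnaires after leaving is stated only for parents who decide to interrupt participation.
- **Outcomes {12}.** The primary criterion is the variation of the Aggressive behavior "score of the CBCL between baseline and month 6 post-intervention".
- **Missing data {20c}.** Markov chain Monte Carlo imputation with 15 cycles, "under the hypothesis of a Missing at Random (MAR) or Missing Completely at Random (MCAR) mechanism".
- **Statistical methods {20a}.** Intention to treat.

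**The concern.** Staff who remove a child for aggression cannot tell from this text whether to keep collecting outcomes. One section says the child leaves the trial, another says only the intervention stops, and a third does not recognise behaviour as a study exit. The only stated request for questionnaires after leaving does not clearly cover a removal that starts with the team.

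The ambiguity falls on children whose behaviour is close to what the primary outcome measures. Removal under {30} follows behaviour that persists during the sessions, that is, between T1 and T2. A child who then leaves the trial has neither a T2 nor a T3 score, so T1 is the only CBCL Aggressive behavior score left to inform imputation. The case report form described in {18a} records attendance and reasons for absence at each session, but lists no rating of in-session behaviour. MAR is doubtful for such a child.

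Removal rates could differ by arm. CBT is led by a psychologist with a nurse or educator, TBI by two nurses or special educators, and all leaders know the allocation.

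**Working it through.** **1. The plan's own figure.** Sample size {14} gives expected month-6 scores of 65 and 69 (difference 4), SD 5.5, alpha 5% and power 80%. Two-sided, normal approximation: n = 2 × (1.96 + 0.84)² × 5.5² / 4² = 29.6, so 30 per group. The t-test version gives 30.67, so 31, as stated. Then 31 × 1.10 = 34.1, so 34 per group and 68 in total. The loss allowance is therefore 34 − 31 = 3 children per arm.

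**2. Shift in the between-arm difference.** Inputs: 34 children per arm (from {14}); k = excess of removed, unobserved children in one arm over the other (assumed); g = true T3 score minus imputed score for such a child, taken as equal in both arms (assumed). T1 is observed, so an error in T3 carries over in full to the change score.

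Shift = k × g / 34, with g from 0.5 SD (0.5 × 5.5 = 2.75) to 1 SD (5.5):

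| k | g = 2.75 | g = 5.5 | Share of the 4-point target |
|---|---|---|---|
| 3 | 3 × 2.75 / 34 = 0.24 | 3 × 5.5 / 34 = 0.49 | 6 to 12% |
| 5 | 5 × 2.75 / 34 = 0.40 | 5 × 5.5 / 34 = 0.81 | 10 to 20% |

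The arm with more removals looks better than it is. Excess removals in CBT enlarge the apparent benefit of CBT; excess removals in TBI shrink it. With k = 0 the shift is zero.

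**3. When MAR imputation fails.** Large-sample simulation with SD 5.5, true difference −4.0 (CBT minus TBI), assumed T1–T3 correlation 0.5 or 0.7, and regression imputation on T1 within arm:

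| What drives removal | 10% removed in each arm | 5% CBT, 15% TBI | 15% CBT, 5% TBI |
|---|---|---|---|
| T1 score only | −4.0 | −4.0 | −4.0 |
| T1, T3 score and noise | −4.0 | −3.5 to −3.7 | −4.3 to −4.5 |
| T3 score alone (extreme) | −4.0 | −3.2 to −3.4 | −4.6 to −4.8 |

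In the first row both arm means are also recovered. In the second and third rows at 10% per arm, each arm mean looks better by about 0.3 to 0.5 and 0.6 to 0.9 points respectively, but the difference does not move. Bias in the treatment comparison thus needs two things together: removal that depends on aggression missing from the observed scores, and a removal share or severity that differs by arm.

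**The case against.** The best defence is that {30} is loosely worded. It ends by speaking of the program, which agrees with {11b}; the exclusion-criteria section leaves no room for a behavioural study exit; and intention to treat is stated. On that reading the child leaves the group and stays in follow-up. The general retention measures in {18b} are not limited to children still attending, and parents take part in the removal decision. The score also remains obtainable: "The CBCL is a 118-item parent-completed questionnaire to measure emotional and behavior problems", and "The child presence is not required for all the measures collected during these assessments". This stands as far as it goes. Missing scores are possible, not certain. It does not remove the conflict, because staff acting on the opening of {30} would have the text on their side.

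Four stronger readings are tempting and are not supported:

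- A reader might infer that each arm's result automatically improves as its most aggressive children leave. MAR imputation corrects for aggression that the observed scores capture, {20c} does not fix the imputation model, and aggression in sessions is not the same measure as a parent rating covering six months.
- A reader might infer a bias favouring CBT. The documents give no removal rate for either arm, and the decision is not left to the group leaders alone.
- A reader might infer that intention to treat is undone. Multiple imputation keeps every randomised child in the assigned arm; the principle is weakened by avoidable missing data, no more. The analysis that directly drops children removed before two thirds of the intervention is the per-protocol one in {20c}.
- A reader might assume a larger gap, such as 8 points, giving 0.71 points for three excess removals and 1.18 for five. That gap is 8 / 5.5 = 1.45 SD beyond a value already adjusted for observed data, and nothing in the documents supports it.

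A sensitivity analysis departing from MAR may also sit in the analysis plan, which is not shown.

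**Conclusion.** The contradiction between the exclusion-criteria section, {11b} and {30} is established from the text, as is the narrow wording of the request in {18b}. The bias is conditional. If {30} is followed literally, T2 and T3 scores may be lost for reasons related to the primary outcome, and imputation under MAR or MCAR could then bias the between-arm difference under the two conditions shown above, in a direction the documents do not determine.

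The size is moderate: about 0.24 to 0.49 points for three excess removals in one arm and 0.40 to 0.81 for five, against a 4-point target. These figures rest on an assumed gap of 2.75 to 5.5 points and assumed removal counts. Five of 34 is 15% of an arm, more than the plan's whole 10% loss allowance, so the upper figures describe an unfavourable case. The point is worth correcting because the remedy is cheap and the data concern the primary outcome.

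**What to change.** 1. Reconcile the exclusion-criteria section, {11b} and {30} so that leaving the group is recorded as discontinuation of the intervention and does not end outcome follow-up. No position is taken on when or why a child should leave the group.
2. Extend the request in {18b} for T2 and T3 questionnaires, including telephone completion, to every removed child, whoever initiated the removal.
3. Report removals by arm.
4. As a secondary request, if the analysis plan does not already contain one, add a sensitivity analysis that departs from MAR for removed children whose scores are still missing.

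The cost is some wording and a few extra questionnaires through an existing procedure. The trial status section says children were still attending groups, and {21b} defers analysis until all visits are complete, so scores not yet due can still be secured.

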### Outcomes {12}

Primary and secondary outcomes will be evaluated in the two groups (TBI and CBT) at the inclusion visit (baseline), at the end of intervention, and at month 6 after the end of the intervention.

The primary judgment criterion is the variation of the “Aggressive behaviors” score of the CBCL between baseline and month 6 post-intervention. The initial evaluation will be on outcomes at month 6 post-intervention; because we hypothesize that the effectiveness of such programs is observed several months after their end. Usually, it takes time for children and parents to assimilate and routinely implement the new techniques and also to observe the intervention benefits in the daily life. This will allow also assessing whether the beneficial effects of the interventions are maintained in the long term.

Secondary judgment criteria include also the variation between baseline and month 6 post-intervention of the CBCL A-A-A score, CBCL-Internalizing and CBCL-Externalizing scores, KIDSCREEN-27, Parental Quality of Life and Developmental Disorder (Par-DD-Qol), Children’s Global Assessment Scale (C-GAS), Parenting Stress Index-Short Form, 4^th^ edition (PSI-4-SF), Beck Depression Inventory-II (BDI-II), and Strengths and Difficulties Questionnaire (SDQ) and the SDQ-dysregulation profile (SDQ-DP).

Exploratory analyses will be realized and will concern the variation of primary and secondary judgment criteria between baseline and at the end of the intervention. Exploratory analyses will be realized to identify possible mediators concerning personality traits on therapeutic effects (response to treatment at T2).

Other data will be collected during the initial visit: presence or absence of psychiatric disorders in children using the K-SADS-PL diagnostic tool, sociodemographic data, anamnestic data, and medication history. Pharmacological treatments will be recorded at each visit because the introduction of a new drug or the modification of posology may influence the research outcomes. Indeed, ADHD usual treatment effectively reduces ED ([28, 46, 86]; Gamli et al., 2018 [97];). The Hierarchical Personality Inventory for Children (HiPIC) will be completed at the end of the intervention to limit the duration of the initial visit.

Means, standard deviations or frequencies, median and percentages will be calculated in order to describe sociodemographic and clinical variables of the sample as well as primary and secondary outcomes.

### Participant timeline {13}

Outcome measures are collected at pretreatment (T1), just after treatment end (T2), and at month 6 post-treatment (T3) (Table 1). Data for the primary and secondary outcomes will be collected at child psychiatry unit of Montpellier University Hospital (MPEA Saint Eloi). The child presence is not required for all the measures collected during these assessments.

**Table 1 Tab1:** Visits and data acquisition during the trial

Timepoint	Study period			
	Enrollment	Before the intervention (T1)	At the intervention end (T2)	Six months after the intervention (T3)
**Enrollment:**				
Eligibility criteria	X			
Child Behavior Checklist (CBCL)	X			
Informed consent	X			
Randomization	X			
**Assessments:**				
Structured clinical interview (K-SADS-PL)		X		
*Parent-rated measures*				
Child Behavior Checklist (CBCL)		X	X	X
Strengths and Difficulties Questionnaire (SDQ-Par)		X	X	X
Behavioral Rating Inventory of Executive Function (BRIEF)		X		X
Hierarchical Personality Inventory for Children (HiPIC)			X	
Kidscreen-27		X	X	X
Parental Quality of Life and Developmental disorder in their children (Par-DD-Qol)		X	X	X
Parenting Stress Index 4^th^ edition (PSI-4-SF)		X	X	X
Beck Depression Inventory-II (BDI-II)		X	X	X
*Child-rated measures*				
Kidscreen-27		X	X	X
*Teacher-rated measures*				
Strengths and Difficulties Questionnaire (SDQ-Teacher)		X	X	X
*Clinician-rated measures*				
*Children’s* Global Assessment Scale (C-GAS)		X	X	X
**Satisfaction questionnaires:**				
*Parent-rated measures*				
Satisfaction questionnaire on the parent program			X	
Satisfaction questionnaire concerning the child program			X	
*Child-rated measures*				
Satisfaction questionnaire on the child program			X	

#### Pretreatment visit (T1)

Participants and their parents will participate in a visit to determine their eligibility (Enrollment, Table 1). Then, the T1 visit takes approximately 2 h, because the diagnostic interview (K-SADS-PL) is carried out systematically with the parents to confirm the diagnosis of ADHD and the presence of comorbidities. During this visit, parents are interviewed by clinicians for clinical ratings of their child’s overall functioning impairment (C-GAS). Children and parents will also complete self-report questionnaires (see Table 1). A questionnaire (SDQ-Teacher) is completed also by the child’s teacher. This questionnaire is either given to parents who will directly transmit it to the teacher, or sent by mail.

